Aim 1: Determine the clinician-reported feasibility of conducting a clinician-level, randomized controlled trial of TLT compared to usual care in the ED.

Hypothesis: TLT is feasible to conduct a clinical-level randomized study in the ED.

Aim 2: Determine the patient-reported acceptability of TLT in the ED.

Hypothesis: The patients or surrogates (if patients are unable to consent) randomized to TLT will feel more heard and understood about their end-of-life care wishes (primary outcome).

1. **GENERAL DESCRIPTION OF THE STUDY DESIGN**

Overview

To demonstrate the feasibility (Aim 1) and acceptability (Aim 2) of TLT, we will conduct a parallel group, clinician-level, pilot randomized clinical trial among 40 emergency clinicians (~20 in TLT and ~20 in usual care) in the ED.

Randomization: Using REDCap’s integrated randomization module,^24^ we will conduct clinician-level randomization using random blocks of four to ensure that emergency clinicians are evenly distributed one-to-one between intervention and control arms.

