**Aim 2: Patient-Reported Acceptability**

Among the patients who were cared by the emergency clinicians enrolled in the randomized trial, we will measure the patient-reported acceptability of the TLT conversations (intervention arm only) and track their clinical outcomes via electronic health record (EHR) review (both intervention and control arms).

1. **SUBJECT SELECTION**

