Outcome Assessments: We will collect the following variables during and after the TLT conversations (Table 2).

For Aim 1 Feasibility, we will collect all outcomes from the intervention arm, and EHR outcome from both intervention and control arms.

For Aim 2 Patient-Reported Acceptability, we will collect all outcomes from both the intervention and control arms.

*For clarity, we placed * on outcomes only collected from the intervention arm.*

| **Table 2. Outcomes and Assessment Timing** | | |
| --- | --- | --- |
| **Aim 1: Feasibility (* indicates outcomes collected only from the intervention arm)** | | |
| **Outcomes** | **Descriptions** | **Timing** |
| Time to complete the TLT conversation (primary outcome)* | With direct observation, the study team will record how long it takes to complete the TLT conversation by the intervenist ED clinician. | At the time of TLT conversation |
| Intervention fidelity* | With direct observation, the study team will record the completion of TLT components using an intervention fidelity checklist. | At the time of TLT conversation |
| Clinician-reported feasibility* | The study team will ask the interventionist emergency clinician to complete two 5-point Likert scale questions (i.e., “How feasible was it to conduct the TLT conversation with your patient?” and “How likely would you recommend the TLT conversation for your colleagues?” “Not at all (1)” to “Completely (5)”). | Immediately after the TLT conversation |
| Recruitment* | The percent that agree to conduct TLT conversations | At enrollment |
| Clinician-reported satisfaction* | The study team will ask the interventionist emergency clinician to complete 5-point Likert scale questions (i.e., “How satisfied are you with the conversation? “Not at all (1)” to “Completely (5)”). | Immediately after the TLT conversation |
| EHR documentation by inpatient clinicians (i.e., intensivists) | Review EHR for new documentation of reference to TLT, serious illness conversation, change in code status, or advance directive forms by inpatient clinicians. | After 24 hours, 48 hours, and 1 week |
| **Am 2: Patient-Reported Acceptability (* indicates outcomes collected only from the intervention arm)** | | |
| **Outcomes** | **Descriptions** | **Timing** |

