| Patient-reported acceptability of TLT conversation (primary outcome)* | A 5-point Likert scale (i.e., “How acceptable was it for your doctor to talk to you about your expectations for ICU care?” and “How likely would you recommend this conversation for other patients like you?” “Not at all (1)” to “Completely (5)”). | Immediately after the TLT conversation |
| Heard and understood | A National Quality Forum endorsed, validated measure for palliative care modified to fit the context of serious illness conversations (“How well they feel heard and understood by your emergency department clinician about medical care they would want if they were to get sicker?” a 5-point Likert scale “Not at all (1)” to “Completely (5)”).^39^ | Immediately after the TLT conversation |
| Patient-reported end-of-life quality of communication | A validated, quality of end-of-life communication survey (4 items selected a priori, a 10-point Likert scale “Worst you can imagine (0)” to “Best you can imagine (10)”).^40^ | Immediately after the TLT conversation |
| Decisional regret scale | A validated survey that measures “distress or remorse after a [health care] decision” (5 items, 5-point Likert scale “Strongly agree (1)” to “Strongly disagree (5)”).^41^ | After 24 hours, 48 hours, and 1 week |
| Clinical outcomes abstracted from EHR | Number of days to the first family meeting in intensive care unit (ICU), ICU length of stay (LOS), hospital LOS, # family meetings, ICU procedures (e.g., CPR, pressors, etc.), ICU mortality, hospital disposition, hospice utilization. | After discharge or upon patient death |

A research assistant blinded to treatment allocation will perform all follow-up assessments. Our team will extract data from the EHR using a standardized approach.^42^

Study Termination:

We will follow the participating clinicians for up to one year to accrue an adequate number of patients they admit to the intensive care unit. Given that an emergency clinician may encounter ~3 to 10 seriously ill older adults being admitted to the intensive care unit per month, we estimate that it would take approximately one year to accrue ~10 patient/interventionist ED clinician who might meet the inclusion/exclusion criteria for Aim 2. The follow-up assessments of the patients will terminate when/if the participants die or are discharged from the hospital.

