**Aim 2: Determine the patient-reported acceptability of TLT in the ED.**

Hypothesis: The patients and surrogates undergoing TLT conversations will feel heard and understood about their end-of-life care wishes (primary acceptability outcome).

Descriptive statistics will be used for baseline characteristics of the study sample. We will compare patient demographics between study arms to assess randomization using two sample t-test or Wilcoxon rank sum test for continuous variables and chi-square for categorical variables. Within arms, we will use a one-sample binomial exact test of proportions for categorical outcomes (e.g., EHR documentation), and Wilcoxon signed ranks test for ordinal outcomes (e.g., Heard and Understood survey). A significance level, alpha, is set to 0.05. We will conduct a secondary analysis using linear mixed models at baseline and one month to include all non-missing data. The EHR-based outcome will be assessed using an EHR review. We will publish our findings regardless of the results and will follow the CONSORT guidelines for reporting RCT.^43^

**Sample Size:** No previous two-arm trial of TLT has been conducted; thus, the effect size remains unknown. Given the primary purpose of conducting a RCT is to demonstrate the feasibility of conducting a randomized design study, no gold standard for sample size calculations exists. However, prior literature suggest that 15 to 20 participants per group are required to ensure scientific validity of the pilot study results.^44^ Therefore, the present study will include a total of 32 participants with 16 participants per group. In addition, the results of this pilot study will provide information on the difference between groups and standard deviation necessary for sample size calculation during the future full-scale study.

1. **MONITORING AND QUALITY ASSURANCE**

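### The protocol names two different Aim 2 primary outcomes: Heard and Understood in the aims and analysis sections, and an intervention-arm-only acceptability measure in Table 2

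*Protocol*

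**What the plan says.** The Aim 2 hypothesis in Specific Aims and Objectives is that patients or surrogates "randomized to TLT will feel more heard and understood about their end-of-life care wishes (primary outcome". The Aim 2 hypothesis in Statistical Analysis keeps the construct but drops the comparison: they "will feel heard and understood about their end-of-life care wishes (primary acceptability outcome".

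Table 2 (Study Procedures, Outcome Assessments) puts the label elsewhere: "Patient-reported acceptability of TLT conversation (primary outcome", followed by an asterisk. The measure consists of two five-point questions, one on how acceptable the talk was and one on whether the respondent would recommend it. The asterisk is defined just above the table: "For clarity, we placed * on outcomes only collected from the intervention arm". Heard and Understood has its own row, beginning "Heard and understood | A National Quality Forum endorsed, validated measure for palliative care modified to fit the context of serious illness conversations", with its own question, no primary label and no asterisk.

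The protocol also disagrees on which arms contribute. The General Description says "we will measure the patient-reported acceptability of the TLT conversations (intervention arm only", and for both arms it mentions only clinical outcomes from the health record. The text introducing Table 2 says "For Aim 2 Patient-Reported Acceptability, we will collect all outcomes from both the intervention and control arms".

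**The concern.** The two candidates are different instruments and answer different questions. Heard and Understood, unstarred in Table 2, could be compared between randomised arms. The acceptability measure asks about a conversation held only in the intervention arm, so it can only be described there.

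The label therefore decides what kind of result Aim 2 reports. With the text as it stands, a report could present either outcome as the prespecified primary and cite the protocol for it, including after both results are known. The trial commits to CONSORT reporting, which makes an unambiguous primary outcome matter even in a pilot.

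**Working it through.** No power or error-rate calculation applies, so the check sets the passages side by side.

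**1. Which outcome is labelled primary for Aim 2?**
- Specific Aims: Heard and Understood, worded with *more*.
- Statistical Analysis, Aim 2: Heard and Understood, without *more*.
- Table 2: the two-question acceptability measure, intervention arm only.

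The analysis section's phrase *primary acceptability outcome* does not merge the two, because Table 2 lists them in separate rows with different questions. All three statements are current Version 1 text.

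**2. Does the sample size show which was meant?** The stated size reproduces: 16 per group × 2 groups = 32, and 16 lies within the cited guide of 15 to 20 per group. The protocol says that the effect size is unknown and gives no SD or power. The figure is tied to neither outcome and does not settle the question.

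**3. Can each candidate do what the protocol asks?**
- The aims ask whether TLT patients feel *more* heard. That needs both arms, and the starred measure has only one.
- The sample size paragraph says that the pilot will supply a between-group difference and an SD for a later trial. A one-arm measure can supply an SD but no between-group difference.
- Heard and Understood could supply both, provided that control-arm patients are surveyed.

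**4. Does the planned analysis settle it?** No. For ordinal outcomes, with Heard and Understood as the example, Statistical Analysis names a within-arm Wilcoxon signed-rank test. A within-arm test does not address a difference between arms. The only between-arm comparison that the section spells out is of patient demographics.

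**5. Do the procedures settle it?** No. Subject Selection says that Aim 2 subjects come from both arms, which suggests that control-arm surveys are intended. Yet its Recruitment part and the Consent Process in Subject Enrollment place the approach and consent after a completed TLT conversation. Table 2 times the Heard and Understood question to the same event. Control-arm patients have no such conversation, so no moment for their consent or survey is given.

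**The case against.** The strongest reply is that this is a pilot. Its stated purpose is feasibility and acceptability, the Aim 1 primary outcome is consistent and has a threshold, and the sample size depends on neither Aim 2 candidate. Aim 2 is itself titled as acceptability, which gives the Table 2 label some support. An SAP or a registration that is not at hand might fix the choice.

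Part of this stands. The consequences are smaller than in a confirmatory trial, and the documents do not force the choice of Heard and Understood. But a later document would have to overrule one part of the protocol: this is two conflicting answers, not a detail left open.

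Four stronger readings are tempting, and the documents do not support them:
- A reader might infer an inflated false-positive rate from two primary tests at 5%. The protocol plans no such pair of tests, and the acceptability measure has no comparator or stated null value. One respondent also answers both instruments at about the same time, so independence would be implausible.
- A reader might infer that relabelling Heard and Understood makes Aim 2 a randomised comparison. It does not while the named test is within-arm. Nor does it remove selection: intervention-arm respondents are consented only after the conversation, whichever outcome is primary.
- A reader might count the lack of an Aim 2 success threshold, next to those for Aim 1, as a further error. A threshold may sit in the SAP.
- A reader might infer an intention to choose the favourable result. The text leaves room for that and shows no such intention.

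**Conclusion.** The contradiction holds. Two sections name one Aim 2 primary outcome, Table 2 names another, and no passage reconciles them. The outcome that Table 2 labels cannot test the hypothesis in the aims or yield the between-group difference promised for the next trial.

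The finding concerns one of the trial's two aims and leaves the Aim 1 primary outcome untouched. It has no numerical magnitude and rests on no modelling assumption. It assumes only that the asterisk means what the protocol says it means, a reading that the General Description supports. It warrants correction before data are seen, because the ambiguity can no longer be resolved neutrally once results are known.

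**What to change.** Before data are seen, name one Aim 2 primary outcome in identical words in Specific Aims, Table 2 and Statistical Analysis. Heard and Understood is the natural choice, since the aims and the analysis section both name it. Acceptability would then be an intervention-arm, descriptive secondary outcome. A threshold for it, such as more than 70% rating 4 or 5 by analogy with Aim 1, is optional.

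If Heard and Understood is primary:
- carry the comparative wording of the aims into Statistical Analysis;
- replace the within-arm signed-rank test for this outcome with a between-arm comparison that accounts for randomisation by clinician, since several patients may share one clinician;
- reconcile the General Description, the text introducing Table 2 and the asterisk on which arms are surveyed;
- state how and when control-arm patients or surrogates are consented and surveyed, with a time anchor that does not depend on a TLT conversation.

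If acceptability is kept as primary instead, the aims and analysis wording must change to a one-arm description, and the sample size paragraph must say which outcome will supply the between-group difference.

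Aligning the labels takes a few text edits. The control-arm consent and survey steps are more than wording: they need a protocol amendment and staff time, and may mean data collection that the current procedures do not describe. Any registration should be brought into line.

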1. *Who is responsible for identifying and recruiting individuals?*

🡪 Upon identification of potential subjects, our research team member (e.g., research assistant) will approach the interventionist emergency clinicians to see if his/her patient can be recruited for this study to confirm the inclusion/exclusion criteria.

1. *When and where individuals are recruited?*

🡪 Potential subjects will be recruited in the ED while receiving care.

🡪 After the intervention emergency clinician completes the TLT conversation, our research team member (e.g., research assistant) will approach the potential subjects or the surrogate for enrollment and completion of the patient-/surrogate-reported acceptability outcomes in the ED.

1. *How recruitment goals match the prevalence rates of the condition/disease being studied and the populations most impacted by the condition/disease being studied?*

🡪 We will recruit from all patients arriving in the ED, which will reflect the prevalence rates of seriously ill older adults in the ED.

1. *Methods to enhance enrollment of diverse individuals and under-represented populations*

🡪 We will cap enrollments of non-Hispanic Whites at 70% of the enrollment target and overenroll other under-represented minorities.

1. **SUBJECT ENROLLMENT**

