**Aim 2: Patient-reported Acceptability**

Pre-screening: We will identify potentially eligible patients using the ED track board in the EHR.

Consent Process:

1. Upon completion of TLT conversation by the interventionist emergency clinician (who also provides clinical care for the patient), our study team (e.g., research assistant, PI) will obtain verbal, informed consent from the patient or surrogate (if applicable) in the ED.
2. The capacity to consent the patient or surrogate is determined by the interventionist emergency clinician who conducted the TLT conversation.
3. **STUDY PROCEDURES**

**Intervention:** Clinician-led conversations about patient’s values and goals, potential benefits and risks of intensive care, and anticipated outcomes are standard of care in the ED. TLT is a multi-modal intervention that provides patient-centered structures to this standard of care. In this evaluation of TLT in the ED, the intervention components will include: 1) a structured conversation guide; 2) clinician training to use the guide; 3) electronic health records (EHR) template for documentation; and 4) standardized communication with the intensivist (**Fig 1**).

1. The TLT Conversation Guide: The structured conversation guide entails discussing patients’ values and goals, prognosis, and shared decision-making to use a trial of intensive care. Originally used in ICU settings,^21, 22^ we systematically refined the guide to be used in the ED incorporating inputs from patient advisors’ and emergency clinicians’ inputs (Appendix).
2. Clinician Training: Leveraging the study team’s expertise in serious illness communication training, the clinician training will include a one-hour didactic on research methodologies and serious illness communication skills, followed by a four-hour communication training with trained actors. Similar training has been described previously.^36-38^
3. EHR Documentation: An Epic template for documenting the TLT conversation findings has been developed (Appendix).
4. **
[figure not shown]
**Intensivist Communication: A standard template to communicate the TLT conversation findings to the intensivists has been developed (Appendix).

Control Group: Emergency clinicians assigned to the control group will not receive the TLT training/guide. Patients cared for by the control group emergency clinicians will receive usual care in the ED. No restrictions will be placed on serious illness conversations in the control group.

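### The blinding claim for all follow-up assessments cannot be assured for the two-arm EHR-documentation outcome, where the reviewer must look for TLT in the chart

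*Protocol*

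**What the plan says.** In the protocol's Study Procedures, under Outcome Assessments, the text after Table 2 reads "A research assistant blinded to treatment allocation will perform all follow-up assessments". It names no exception. The next sentence is "Our team will extract data from the EHR using a standardized approach", which neither claims nor excludes blinding.

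Table 2 lists two outcomes timed at 24 hours, 48 hours and 1 week. One is the decisional regret scale, a survey. The other, under Aim 1, is EHR documentation by inpatient clinicians: "Review EHR for new documentation of reference to TLT, serious illness conversation, change in code status, or advance directive forms by inpatient clinicians". It covers both arms: "For Aim 1 Feasibility, we will collect all outcomes from the intervention arm, and EHR outcome from both intervention and control arms".

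A further set of chart outcomes under Aim 2 is taken once the patient has left hospital or died. It begins "Number of days to the first family meeting in intensive care unit (ICU), ICU length of stay (LOS), hospital LOS, # family meetings" and goes on to ICU procedures, ICU mortality, disposition and hospice use.

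The Intervention text in the same section lists four components. Two of them leave or prompt a written trace: an Epic template for the TLT note, and a standard template for passing the TLT findings to the intensivists. Control clinicians get no TLT training or guide, but their serious illness conversations are not restricted.

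**The concern.** Blinded assessment is worth claiming only where the assessor cannot readily learn the arm. Here the assessor is told to search for the name of the intervention, in a record where the intervention leaves a labelled note.

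The outcome also takes judgement. Someone has to decide whether an intensivist's entry amounts to a serious illness conversation, and the protocol does not define this. An abstractor who knows the arm may read borderline entries in favour of TLT.

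The Statistical Analysis section names EHR documentation as its example of a categorical outcome for testing. The sample size paragraph says the pilot will supply the between-group difference for sizing a full trial. A biased difference could therefore carry forward, while a report following CONSORT would describe the assessment as blinded.

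**Working it through.** No arithmetic applies. The check compares the blinding sentence with each outcome it might cover.

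**Step 1. Is the EHR-documentation review a follow-up assessment?** It has the same three time points as the regret scale, and all three fall after the ED encounter. On an ordinary reading, *all* includes it. The sentence on EHR extraction, with its change of actor from the blinded assistant to the team, allows the opposite reading.

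**Step 2. Does the outcome show the arm?**

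| Outcome or element | Names the intervention? | Can occur in both arms? | Room for judgement |
| --- | --- | --- | --- |
| Mention of TLT in inpatient notes | Yes | Possible, but unlikely in control | Some |
| Serious illness conversation | No | Yes | Considerable |
| Change in code status | No | Yes | Little |
| Advance directive form | No | Yes | Little |
| Family meetings (first meeting, count) | No | Yes | Considerable if taken from notes |
| Length of stay, ICU mortality | No | Yes | Little |
| Decisional regret survey | No | Yes | Scored by the respondent |

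The last two columns are my reading of the definitions. The first four rows make up the EHR-documentation outcome, and one of the four names the intervention.

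**Step 3. What else in the chart shows the arm?** When a TLT conversation has been documented, the ED template note is in the same record. The reviewed inpatient notes are written after the intensivists have received the TLT message. Randomization is by clinician, so a reviewer who knows who was trained could also infer the arm from the treating ED clinician's name. That last route assumes the name is visible in the chart.

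**Step 4. Is there a safeguard?** The protocol describes no redaction of the ED note, no masking of the treating clinician and no separate abstractor. The study team observes and times TLT conversations. Afterwards, "our research team member (e.g., research assistant) will approach the potential subjects or the surrogate for enrollment". Nothing says that this person is different from the blinded assistant.

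**Step 5. What does each reading of the scope give?** If *all* includes the chart review, the protocol claims a blinding it gives no means of achieving. If it does not, the word is too broad and the abstractor's blinding is left unstated. Both readings call for the same edit.

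**The case against.** The strongest reply is that the blinding sentence was never meant to reach the chart. The next sentence changes the actor and claims no blinding. The Study Termination text ends follow-up assessments at death or discharge, which is when the Aim 2 clinical outcomes begin. This largely stands: those clinical outcomes lie outside the term as the protocol uses it, and for the earlier chart review the fault may be unclear scope rather than a false statement.

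A reader might infer that the chart outcomes reveal the arm by definition, so that no blinding exists for any of them. The protocol does not support that. Only one element names TLT, and even that is not decisive: an intensivist could write of a TLT for a control patient, and an intervention patient's inpatient notes may never mention it. The review is aimed at inpatient notes, so seeing the ED template would be incidental. No Aim 2 clinical outcome names the arm.

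It is also fair to say that observing the conversation and asking the acceptability items happen in the ED and are not follow-up. Nothing shows that the same person does both jobs. The point is only that nothing keeps them apart.

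Finally, the consequence is limited. Both outcomes marked primary in Table 2 come from the intervention arm only, at or just after the conversation. The heard-and-understood item, which the Aim 2 hypotheses call primary, is also asked at that time and is not a chart outcome. None of the three feasibility thresholds uses chart data. The test named for EHR documentation is a within-arm binomial test, not a comparison of arms. All of this stands, and it keeps the point to a secondary outcome.

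**Conclusion.** The concern holds in a limited form. For the two-arm EHR-documentation outcome at 24 hours, 48 hours and 1 week, blinding cannot be assured as the protocol describes it, and the text does not settle whether that outcome is inside the claim. Note-based family-meeting counts share the exposure through incidental sight of the TLT note. Length of stay and mortality are little exposed.

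The size of any detection bias cannot be derived from the document. The primary outcomes are not affected. The conclusion assumes that the reviewer works from the open chart and that completed TLT conversations are documented in the template. The correction is worth making because it decides what the trial may report as blinded.

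**What to change.** 1. Limit the blinding statement to the decisional regret surveys. Have them done by a team member who did not observe or enrol that patient in the ED. By the same reasoning, that person should not have reviewed the patient's chart beforehand.
2. State who abstracts the EHR data. State that the EHR-documentation outcome, and any family-meeting count taken from notes, is abstracted unblinded against definitions written beforehand, and do not report these items as blinded.
3. Take objective outcomes, such as length of stay and mortality, from structured fields where these exist.

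The cost is mainly wording. The stated blinding becomes less favourable. The separation of roles assumes that more than one team member is available, and the protocol does not give the number.

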Experts agree that serious illness care should focus on preparing people for and then supporting them in in-the-moment decision-making during clinical deterioration.^14-16^ Medical crises exemplify the most challenging, in-the-moment decision-making. During medical crises, **time-limited trials (TLT)** are a recommended approach to reducing potentially nonbeneficial treatments for seriously ill older adults.^17-19^ TLT is a structured conversation between clinicians and patients/surrogates to discuss patients’ values and preferences, prognosis, and shared decision-making to use specific therapies for a prespecified period of time. TLT allows both clinicians and patients/surrogates to regularly assess if therapies are meeting patients’ goals over structured time intervals. Guided by the Capacity, Opportunity, Motivation to perform a Behavior (COM-B) framework,^20^ a quality improvement study of TLT in the ICU (N=209) was associated with a 35% increase in formal family meetings (p<0.01), 45% increase in clinicians eliciting values and preferences of patients (p<0.01), 1.3 day decrease in median ICU length of stay (p<0.02), and 13% decrease in mechanical ventilation (p=0.02). No change in hospital mortality was observed (58.4% vs. 58.3%, p=0.99).^21, 22^ TLTs have been published as an expert recommended approach in the official journal of the American College of Emergency Medicine.^23^ Although decisions to initiate intensive care occur in the ED, no study has evaluated the effect of TLT initiated in the ED.

The objective is to assess the feasibility and acceptability of TLT initiated in the ED. We will conduct a pilot randomized trial of TLT on seriously ill older adults starting intensive care in the ED. Rationale: Initiating TLT at the first moment of starting intensive care in the ED may further improve patient-centered outcome compare to the usual care (no TLT). Our central hypothesis is that TLT can be successfully initiated in a randomized study design in the ED.

**Impact:** We anticipate that introduction of TLT in the ED will lead to improved patient-centered utilization of intensive care for seriously ill older adult. If TLT is found to be feasible and acceptable in the ED, the potential exists to standardize the most challenging, in-the-moment decision-making for seriously ill older adults to improve their quality of end-of-life care nationally.

1. **SPECIFIC AIMS AND OBJECTIVES**

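### Decisional regret is due up to 1 week, but patient follow-up ends at death or discharge, so the 1-week score covers only patients alive and still in hospital

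*Protocol*

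**What the plan says.** In the protocol's Study Procedures, the Aim 2 part of Table 2 lists the decisional regret scale (5 items, each scored 1 to 5) with the timing "After 24 hours, 48 hours, and 1 week". The row carries no asterisk, the mark for outcomes taken only in the intervention arm. The text above the table says: "For Aim 2 Patient-Reported Acceptability, we will collect all outcomes from both the intervention and control arms". Regret is therefore due in both arms at all three times.

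The Study Termination paragraph then states: "The follow-up assessments of the patients will terminate when/if the participants die or are discharged from the hospital". Nothing in the protocol exempts regret from this rule, plans contact after discharge, or limits the 1-week score to inpatients.

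Three other places bear on the point:

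- Table 1 (Subject Selection) makes the surrogate the respondent when the patient cannot consent. It gives no proportions.
- The clinical outcomes row of Table 2 includes "ICU length of stay (LOS), hospital LOS", together with hospital disposition and hospice use.
- Statistical Analysis, Aim 2, plans a secondary linear mixed model on all non-missing data at baseline and one month. One month is not an assessment time in Table 2.

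**The concern.** The schedule asks for a score at 1 week from every respondent, and the termination rule withdraws it from anyone whose patient has died or gone home. Being alive and in hospital at day 7 is determined after randomisation. A 1-week regret mean built on that condition describes longer-stay survivors, not the enrolled group. Those whose patient left early or died contribute nothing at that time, and their view of the decision may well differ.

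Two uses of the pilot are affected. The Sample Size paragraph wants the pilot to supply between-group differences and standard deviations for a full-scale study, and at 1 week these would come from a selected subset. The 1-week completion rate would also reflect the rule and the length of stay, so it would say little about whether respondents are willing to answer. This cannot be left to the analysis, because no model recovers scores that were never collected. A mixed model on non-missing data would treat exit from hospital as ignorable and would treat a score after death as merely missing.

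**Working it through.** **The text.** Schedule: 24 hours, 48 hours and 1 week, both arms. Stop rule: death or discharge, whichever comes first. The two agree only for patients whose stay exceeds the assessment time. For everyone else the schedule requires a score and the rule forbids it.

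**The plan's own figure.** The protocol gives no number assessable for regret at any time. Its sample size is 2 × 16 = 32, from a pilot rule of thumb of 15 to 20 per group. That arithmetic agrees. The paragraph does not say whether these participants are clinicians or patients, so 16 per arm serves below only as an illustrative denominator.

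**Share still in hospital.** Assumptions, none of them in the documents:

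- time to death or discharge is lognormal with log-SD 0.8;
- the control median is 5, 7, 10 or 14 days;
- the TLT median is 1.3 days shorter. This borrows the ICU figure in Background and Significance and applies it to hospital stay, which the protocol does not do.

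Formula: P(in hospital at t) = 1 − Φ((ln t − ln median)/0.8). Example, median 7, t = 7: 1 − Φ(0) = 50%. Median 5.7: 1 − Φ(0.257) = 40%.

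| Control median (days) | 48 h, control vs TLT | 1 week, control vs TLT | Of 16 per arm at 1 week |
|---|---|---|---|
| 5 | 87% vs 78% | 34% vs 21% | 5.4 vs 3.4 |
| 7 | 94% vs 90% | 50% vs 40% | 8.0 vs 6.4 |
| 10 | 98% vs 97% | 67% vs 61% | 10.8 vs 9.7 |
| 14 | 99% vs 99% | 81% vs 77% | 12.9 vs 12.3 |

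At 24 hours the share is 95% or more throughout. The 1-week loss runs from 100 − 81 = 19% to 100 − 21 = 79%, that is, roughly 20% to 80%.

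**A second curve.** With exponential exit times, P = 0.5^(7/median). The 1-week shares are 38% vs 27%, 50% vs 43% and 62% vs 57% for control medians of 5, 7 and 10 days, and 0.5^(7/14) = 71% vs 0.5^(7/12.7) = 68% for 14. These losses lie within the same range. This curve puts more exits early: at a control median of 5 days the 48-hour share is 0.5^(2/5) = 76% vs 0.5^(2/3.7) = 69%. The small early loss in the table therefore depends on the lognormal shape.

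**Effect on the scores.** A simulation set the true effect on regret to zero, with SD 20 on a 0 to 100 scale and correlation 0.2 or 0.4 between regret and log time to exit (all assumed). For control medians of 5 to 10 days, the 1-week mean within an arm moved 2.2 to 10.9 points from the mean of all patients. The false difference between arms was 0.4 to 2.2 points. For scale, the standard error of a difference with 16 per arm is 20 × √(1/16 + 1/16) = 7.1 points. Selection within each arm is the larger effect.

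**The case against.** A reader might infer that TLT is expected to change who is still in hospital at 1 week, so that the comparison between arms is biased. The documents do not support that as stated. The cited "1.3 day decrease in median ICU length of stay" concerns ICU stay in a quality improvement study, and a patient moved from the ICU to a ward is still in hospital. The same study saw no change in hospital mortality (58.4% vs 58.3%), so the level of about 58% is not evidence that TLT alters survival. The protocol's own expectation is "We anticipate that introduction of TLT in the ED will lead to improved patient-centered utilization of intensive care", which does not predict earlier discharge. Listing hospital stay as an outcome does not predict a change in it either.

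A reader might also infer that surrogates are certainly dropped. The sentence speaks of assessments of the patients and ends them when participants die or leave. It can be read either way for a surrogate respondent, and that ambiguity itself needs settling.

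Regret is not marked as a primary outcome. Both outcomes so marked in Table 2 are measured during or immediately after the conversation. For ordinal outcomes the Statistical Analysis names a within-arm signed-rank test, and no between-arm test of 1-week regret is specified. The size of the loss rests wholly on assumed stays, and at a 14-day median it is only 19% to 23%.

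All of this stands, and it limits the point. It does not remove the conflict between schedule and stop rule, nor the selection within each arm at 1 week, which needs no effect of TLT on length of stay.

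**Conclusion.** The concern holds as a conflict within the protocol that limits one non-primary outcome. The 1-week regret score, as planned, comes only from patients alive and still in hospital, with an unstated position for surrogates. The 48-hour score is touched to a smaller degree, and the 24-hour score little unless early exits are common. The loss at 1 week is roughly 20% to 80% under assumed control medians of 5 to 14 days. The documents offer no distribution that would narrow this. Selection within each arm follows directly from the text whenever regret is related to length of stay or death. Unequal selection between arms is possible, but it is not shown, and it was small under the assumptions tried. The change is worth making because the pilot is meant to inform a full-scale study and the missing scores cannot be recovered later.

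**What to change.** Reword Study Termination along these lines: discharge does not end decisional regret assessment; respondents whose patient has been discharged are telephoned at the remaining times up to 1 week. State explicitly whether an enrolled surrogate is still invited after the patient's death and, if so, that refusal is easy. Report the number assessed at each time by arm and by discharge and vital status. Reconcile the one-month time in the Aim 2 analysis with Table 2 in the same edit.

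If contact after discharge is not wanted, define the outcome as regret while in hospital, report the number assessable per arm at each time, and do not read the 1-week result as a comparison of all enrolled respondents.

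Cost: a wording change plus calls by the blinded research assistant who already does the follow-up. Contact information is already linked to study data (Risks and Discomforts). The number of calls at 1 week depends on enrolment. With 16 patients per arm, those no longer in hospital number (16 − 12.9) + (16 − 12.3) ≈ 7 to (16 − 5.4) + (16 − 3.4) ≈ 23 across both arms. If the intended 10 or so patients for each of about 20 intervention clinicians are reached, the TLT arm alone has 200 × 0.23 = 46 to 200 × 0.79 = 158. These are upper limits, because they include deaths. The other downside is possible contact soon after a death, so some scores will still be missing.
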